### Outcomes

As this study is a pilot RCT, the primary outcome is feasibility as measured by adherence (primary), retention, and recruitment rates. Satisfaction with the PT Navigator role will also be used to assess feasibility. Secondary estimates of effect will be measured for health-related quality of life (HRQOL), self-reported exercise volume, health care utilization, activity limitation, exercise capacity, functional strength and overall impairment score. Outcome data will be assessed and collected using REDCap [38] at three timepoints: baseline (T1), post-intervention (T2: 18 weeks), and 2-month follow up (T3). See Fig 2 for the assessment schedule. It will take approximately 45 minutes to complete the required outcome measures. Following consent, participants will complete a baseline demographic questionnaire. The demographic questionnaire will include the Gender Related Attributes Survey (GERAS) [42], cancer characteristics, and prior experience with a PT.

### Feasibility

We selected feasibility outcomes to determine if any modifications would be needed prior to conducting a larger scale trial. A “traffic light” approach [43] was used as criteria for demonstrating feasibility, see Table 2. A “green light” indicates moving forward with no changes, a “yellow light” indicates proceeding with some modifications, and a “red light” indicates that the outcome was not feasible without making significant modifications to our methods [43]. The primary outcome of this study is feasibility as measured by adherence rate [37,44,45]. Criteria for feasibility and threshold details for each outcome are outlined in Table 2. Success thresholds were determined based on prior studies in this field for adherence [46–49], retention [46,47], recruitment [46,50], and a priori by authors for satisfaction rates.

**Table 2 pone.0351761.t002:** Traffic Light Criteria.

Criteria	Traffic Light Criteria		
	Green Light	Yellow Light	Red Light
** *Adherence* **			
Proportion of sessions attended with the PT Navigator	>70% of sessions with the PT Navigator were attended by the participants	50-70% of sessions with the PT Navigator were attended by the participants	<50% of sessions with the PT Navigator were attended by the participants
** *Retention* **			
Proportion of enrolled participants who complete post-intervention and follow-up assessments	>70% of participants complete post-intervention and follow up assessments	50-70% of participants complete post-intervention and follow up assessments	<50% of participants complete post-intervention and follow up assessments
** *Recruitment* **			
Proportion of eligible patients who enrolled into the study	>70% of eligible participants enrolled into the study	50-70% of eligible participants enrolled into the study	<50% of eligible participants enrolled into the study
** *Satisfaction* **			
Proportion of participants who report satisfaction with the PT Navigator role	>75% of participants select 5–7 on a 7-point Likert scale (higher scores indicate greater satisfaction)	50-75% of participants select 5–7 on a 7-point Likert scale (higher scores indicate greater satisfaction)	<50% of participants select 5–7 on a 7-point Likert scale (higher scores indicate greater satisfaction)

### Secondary Effectiveness

***Overall Impairment Score:*** The Edmonton Symptom Assessment System (ESAS) [51] will be used to assess overall impairment. The ESAS is a valid, reliable, and responsive measure in assessing various symptoms in individuals living with cancer [52–54]. Symptoms assessed through the ESAS has evolved to encompass many common cancer-related symptoms including nausea, depression, anxiety, pain, tiredness, drowsiness, shortness of breath, appetite, and well-being [55]. Respondents will be asked to rate their symptoms on a visual analog scale ranging from 0 (i.e., no symptoms) to 10 (i.e., maximal symptoms) [51]. Higher scores represent higher perceived symptom burden [51].

***Self-Reported Exercise Volume:*** The Godin Leisure Time Exercise Questionnaire [56] will be used to assess self-reported exercise volume. This questionnaire asks respondents to classify the amount of mild, moderate, and strenuous weekly activity [56]. It provides a total weekly leisure activity score [56]. Published literature has found the questionnaire to be reliable in classifying individuals living with and beyond cancer as ‘active’ and ‘insufficiently active’ [56–58]. Higher scores represent higher weekly levels of exercise [56].

***HRQOL:*** To measure HRQOL, both the EORTC QLQ-C30 [59] and the Functional Assessment of Cancer Therapy – General (FACT-G) [60] will be used. The FACT-G is a 27 item self-administered questionnaire that measures four domains of HRQOL including physical, emotional, social, and functional wellbeing [61]. The EORTC QLQ-C30 is also a self-administered measure that incorporates five functional scales (physical, social, emotional, role, and cognitive), three symptom scales (pain, fatigue, and nausea/vomiting), global; health status, other common cancer-related symptoms including loss of appetite and insomnia, and perceived financial impact of the disease [62,63]. Both questionnaires are commonly used around the world for individuals living with and beyond cancer, and psychometric evidence does not generally recommend one questionnaire over the other as both demonstrate good reliability, validity, and responsiveness [64].

***Health Care Utilization:*** A piloted healthcare resources survey [65] will be completed by participants in both groups at T2 and T3. This questionnaire assesses loss of work, procedures received, and all health-related visits (i.e., family doctor, support services). All costs will be calculated according to current (2025) Ontario healthcare standards and presented in CAD [65].

***Activity Limitation:*** To quantify activity limitation, the *Patient-Specific Functional Scale (*PSFS) [66] will be used. The PSFS asks respondents to identify three activities they are unable to do or having difficulty with completing [66]. Published literature has found this questionnaire to be a valid, reliable, and responsive outcome measure for use in musculoskeletal conditions [66,67]. Higher scores indicate greater ability to perform the activity at the same level prior to living with cancer [66].

***Exercise Capacity:*** To measure exercise capacity, 6-minute walk test [68] will be used. This performance-based test measures the distance a person can walk in six minutes. This test has been found to be reliable and valid for individuals living with and beyond cancer [69]. Higher distances indicate greater exercise capacity and endurance [68].

***Functional Strength:*** To measure functional strength, the 30 second sit to stand test [70] will be used. The test measures how many times a person can sit-stand-sit in 30 seconds. This test has been found to be valid and reliable in individuals living with cancer [71,72]. Higher repetitions indicate greater functional/lower extremity strength [73].

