## Methods

### Study purpose

The purpose of this pilot RCT is to examine the feasibility of a PT Navigator role for individuals living with cancer receiving cancer treatment in an acute cancer care setting. Specifically, our research questions are as follows:

*Research question 1 (Primary):* Is a PT-Navigator role feasible, as measured by adherence, recruitment, retention, and satisfaction rates, to implement at a cancer institution in Ontario, Canada?

*Research question 2 (Secondary):* Do individuals with cancer who are monitored by a PT-Navigator demonstrate trends for improved outcomes in overall impairment score, health-related quality of life, physical activity levels, exercise capacity, functional strength, activity limitation, and a reduction in health care utilization costs compared to individuals with cancer who are not monitored by a PT Navigator during treatment?

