### Procedure

Intervention Group (PT Navigator). The interactions with the PT Navigator will occur at the JCC. The PT Navigator will follow the PSM [18] for ongoing monitoring and surveillance. The PT Navigator will check-in with participants approximately every two to three weeks over a maximum of 18 weeks (i.e., six sessions total with the PT Navigator) when they are already coming to the JCC for another appointment. Interactions with the PT Navigator will be 30 minutes (follow-ups) to one hour (initial assessment). Fig 3 represents the PT Navigator interaction process.

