The PT Navigator will also assist participants in setting goals and developing action plans focused on functional activity or reduction in symptoms during each visit. Importantly, the PT Navigator will serve as an advocate to ensure the patient feels supported and aware of all resources available to them. The participants allocated to the intervention group will also be given the PT Navigator’s contact information and will be encouraged to communicate with them if they ever have any questions or concerns throughout the intervention period.

Control (Usual Care). Participants in this group will have no interaction with the PT Navigator. They will continue with usual care regarding rehabilitation from their medical oncologist and oncology care team. This ranges from no discussion of rehabilitation to general advice to stay physically active [41]. We will track any interventions received outside of the hospital by all participants (e.g., visits with family doctor, community PT) using the health care utilization questionnaire included as a study outcome.

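### The health care cost comparison does not fix whether the navigator's own sessions count, and two paragraphs give its survey different scopes

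*Protocol article*

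**What the plan says.** Research question 2 (Study purpose) asks whether participants monitored by the navigator show "a reduction in health care utilization costs compared to individuals with cancer who are not monitored by a PT Navigator". It is a contrast between arms.

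The survey behind that contrast is described twice:

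- Procedure, Control (Usual Care): "We will track any interventions received outside of the hospital by all participants", using the health care utilization questionnaire.
- Secondary Effectiveness, Health Care Utilization: the survey covers "loss of work, procedures received, and all health-related visits (i.e., family doctor, support services"), with no restriction to care outside the hospital. On costing it adds: "All costs will be calculated according to current (2025) Ontario healthcare standards and presented in CAD".

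On where the intervention is delivered, the Procedure section says: "The interactions with the PT Navigator will occur at the JCC". It fits the sessions around visits that participants are already making to the centre for other appointments.

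On timing, the Health Care Utilization paragraph says that the survey "will be completed by participants in both groups at T2 and T3". The Outcomes section, which lists health care utilization among the outcomes, says: "Outcome data will be assessed and collected using REDCap [38] at three timepoints", the first of which is baseline.

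**The concern.** A comparison meant to show whether a new service lowers health care costs has to count the cost of the service, or say openly that it does not. Here one description of the survey would leave the navigator sessions out, the other could take them in, and no sentence settles it.

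The wider description is not a full safeguard, because the survey is completed by participants. A session attached to an oncology appointment may not be reported as a visit of its own, so whether the intervention is costed could depend on what each person remembers or considers separate.

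The resource in question exists in one arm only. If it is left out, the intervention arm looks cheaper on that component by construction. The Discussion says the pilot will inform trends in utilization costs, so the result may carry into the case for a larger trial.

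**Working it through.** **The plan's own figure.** The article states no cost figure. Its only calculated figure is the sample size, which supplies the 13 per arm used below. For 70% adherence, a margin of 0.2 and a 95% interval, n = 1.96² × 0.7 × 0.3 / 0.2² ≈ 20.2, against 20 stated. Allowing for 20% dropout, 20 / 0.8 = 25, or 26 as an even total for 1:1 allocation. The stated 13 per group is reproduced.

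**Inputs for navigator time.** The Procedure section gives six sessions per intervention participant: one hour for the initial assessment and 30 minutes for each follow-up. Control participants have no contact with the navigator.

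**Scheduled time that could go uncounted**

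- Per participant at full attendance: 1 + 5 × 0.5 = 3.5 h, against 0 h in control.
- For 13 participants: 13 × 3.5 = 45.5 h.
- At 70% attendance (the adherence assumed under Sample size): 0.7 × 6 = 4.2 sessions. If the initial session is among those attended, 1 + 3.2 × 0.5 = 2.6 h per participant, or 13 × 2.6 = 33.8 h for the arm.

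Contact between visits, which the Procedure section encourages, is not in these figures.

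**In money, under an assumption.** The article gives no hourly cost. For an assumed CAD 50 to 150 per hour:

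| Attendance | Hours per participant | CAD per participant |
|---|---|---|
| Full | 3.5 | 175 to 525 |
| 70% | 2.6 | 130 to 390 |

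For the arm of 13 at full attendance this is 45.5 × 50 = CAD 2,275 to 45.5 × 150 = CAD 6,825. The article gives no expected total cost or spread, so these amounts cannot be expressed as a share of the cost difference.

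**Component in the other direction.** The Procedure section lets the navigator refer participants to community programs and to other disciplines. Visits that follow fall within either description of the survey and raise the counted cost in the intervention arm. Their number cannot be worked out from the article.

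**Effect of having no baseline.** With 13 randomized per arm, the chance difference between arms in prior use has a standard error of √(2/13) = 0.39 SD, centred on zero. A difference of 0.5 SD or more arises with probability 2 × [1 − Φ(0.5/0.392)] ≈ 20%, about 10% in each direction. Adjusting for a baseline value with correlation ρ would multiply the standard error by √(1 − ρ²). For assumed correlations of 0.3, 0.5 and 0.7 the factors are 0.954, 0.866 and 0.714, which are reductions of about 5%, 13% and 29%. The article gives no correlation.

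**The case against.** The strongest reply is that nothing in the article excludes the sessions. The Health Care Utilization paragraph, which defines the outcome, takes in every health-related visit. The sentence under Control may only mention one use of the survey. The instrument is in a cited source that is not at hand, and a condensed article may leave costing rules to a fuller document. This stands so far as it rules out saying that the sessions are omitted, which a reader might infer from the Control paragraph alone. It does not remove the disagreement between the two descriptions, or the doubt about whether participants would report sessions attached to other appointments.

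A reader might also infer that the comparison as a whole is tilted towards a cost reduction. The documents do not support that: referrals push counted cost up in the same arm, and neither component's net contribution is known.

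A third tempting reading is that the lack of a baseline survey adds to the bias. Under 1:1 randomization it does not. Chance imbalance is symmetric, and what is lost is precision. The T2 and T3 timing reads as a specific rule qualifying the general schedule, and measuring resource use over follow-up only is a legitimate choice. The reduction in research question 2 is between arms and needs no baseline value.

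Finally, this is a secondary, descriptive outcome in a pilot of 26 that is not powered for group differences, and cost is not among the traffic-light criteria in Table 2. That limits the weight of the point. The remedy is still worth making because it costs almost nothing.

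**Conclusion.** The point holds as an unresolved scope with a one-sided resource at stake. The two descriptions of the survey differ, and the article does not say whether navigator sessions are costed, although it asks about a cost reduction against control. If the narrower scope is applied, or participants do not report the sessions, the contrast leaves out up to 3.5 h of scheduled physiotherapist time per intervention participant (45.5 h for 13), or about 2.6 h each at 70% attendance with the initial session kept, against none in control. At an assumed CAD 50 to 150 per hour that is CAD 175 to 525 per participant at full attendance.

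The omission would favour the intervention on that component only. The net direction of the cost contrast is not established. The missing baseline is a symmetric loss of precision and calls for no more than a clarification of timing.

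**What to change.** 1. Reconcile the Control (Usual Care) paragraph with the Health Care Utilization paragraph, so that the survey has one stated scope.
2. State that delivered navigator time will be added to each intervention participant's cost from the session attendance records and not from participant report, with the unit cost and its source named. If the survey also captures these sessions, remove them there so that they are not counted twice.
3. Report the between-arm cost difference, with its interval, both with and without navigator time.
4. Show care that follows from navigator referrals as a separate line, so that the two opposing components are visible.
5. In the Outcomes section, say that health care utilization is collected at T2 and T3 only. A baseline survey is optional.

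The cost is slight. Attendance has to be recorded for the primary adherence outcome in any case. The extra work is to choose a unit cost, to match reported visits to the navigator's referral notes, and to run one additional summary. The cost result may look less favourable to the intervention.

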### Analysis

Stata Statistical Software (Version 19) will be used for all statistical analyses [74]. Descriptive statistics including means and standard deviations will be calculated for continuous outcomes. If not normally distributed, medians and quartiles will be reported. Categorical data will be described through absolute and relative frequencies.

Our primary outcome of feasibility will be analyzed using descriptive statistics. As a pilot RCT, we are not powered to accurately assess the effectiveness of the PT Navigator on the specified effectiveness outcomes (i.e., overall impairment score, HRQOL, self-reported exercise volume, activity limitation, exercise capacity, functional strength). Descriptive statistics including means and 95% confidence intervals will be reported to observe trends in all outcomes. We will follow the CONSORT reporting guidelines for extension to pilot trials [32] when reporting our results.

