### Sample size

Our sample size was calculated using a confidence interval approach based on recommendations for pilot trials [35–37]. Specifically, we used a 95% confidence interval, a desired margin of error of 0.2, and our estimated 70% adherence rate to determine feasibility. The calculated sample size was 20 participants. However, to account for a 20% dropout rate, the final sample size will include 13 participants per group (26 total). It is important to consider that as the pilot study is exploratory in nature, this sample size is not powered to detect meaningful change between groups.

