### Randomization and allocation

Randomization will be completed by a member of the research team using RedCap [38]. The 1:1 randomization schedule will be generated using permuted blocks by a member of the research team not involved in recruitment, randomization or treatment delivery. Participants allocated to the intervention group will receive a phone call by the PT Navigator to schedule the first intervention session.

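### The effectiveness analysis names no between-arm difference and no use of baseline values; a baseline-adjusted difference would be more precise at the same sample size

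*Protocol article*

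**What the plan says.** Research question 2 (Protocol article, Study purpose) is comparative. It asks whether monitored participants show better trends "compared to individuals with cancer who are not monitored by a PT Navigator during treatment". The Outcomes section describes the secondary results as estimating effects, and sets the measurement times as "baseline (T1), post-intervention (T2: 18 weeks), and 2-month follow up (T3").

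The Analysis section then gives the method for these outcomes: "Descriptive statistics including means and 95% confidence intervals will be reported to observe trends in all outcomes". The abstract likewise says that preliminary effectiveness will be assessed descriptively. Neither place names a between-arm difference, a model, a change score or a covariate. Neither says whether the intervals belong to arm means or to the difference between arms.

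One outcome has no baseline: the health care survey is completed at T2 and T3 only (Secondary Effectiveness).

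On size and allocation, the article says "to account for a 20% dropout rate, the final sample size will include 13 participants per group (26 total"), "this sample size is not powered to detect meaningful change between groups", and "The 1:1 randomization schedule will be generated using permuted blocks". It states no stratification factor, and any type or stage of cancer is eligible.

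**The concern.** In a two-arm trial an effect is a difference between arms. A table of means with intervals for each arm does not give an interval for that difference, and a reader who judges trends by whether two intervals overlap applies a much stricter criterion than the difference itself would.

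The symptom, exercise, quality-of-life, activity-limitation, walk and sit-to-stand measures are all scheduled at T1, yet the stated analysis gives the T1 value no role in the comparison. Permuted blocks balance the numbers in each arm, not the baseline values. With 13 mixed-diagnosis patients per arm, sizeable chance differences at baseline are to be expected on some measures. What is at stake is how informative the reported trends are when a larger trial is designed. No decision rule of this pilot depends on them.

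**Working it through.** **Inputs from the article.** 13 per arm; 20% dropout, so 13 × 0.8 = 10.4, about 10 per arm; 95% confidence; margin 0.2; adherence 70% (all from Sample size). **Assumption.** The correlation r between baseline and follow-up is not in the article. It is shown for 0.3, 0.5, 0.7 and, where useful, 0.8.

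**1. The plan's own figure.** The article says "we used a 95% confidence interval, a desired margin of error of 0.2, and our estimated 70% adherence rate to determine feasibility". The normal-approximation formula gives n = 1.96² × 0.7 × 0.3 / 0.2² = 20.17. This agrees with the stated 20 (21 if rounded up). Then 20 / 0.8 = 25, raised to 26 for equal arms. The figure reproduces, and it depends on adherence alone.

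**2. Chance baseline imbalance.** In SD units, the baseline difference between arms has standard deviation √(2/n), and P(|difference| > t) = 2 × [1 − Φ(t / √(2/n))].

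| Per arm | SD of difference | P(> 0.2 SD) | P(> 0.5 SD) | P(> 0.8 SD) |
|---|---|---|---|---|
| 13 | 0.39 | 61% | 20% | 4% |
| 10 | 0.45 | 65% | 26% | 7% |

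These are probabilities for one measure.

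**3. Carry-over.** A baseline difference of b shifts the expected unadjusted follow-up difference by r × b. For b = 0.5 SD the shift is 0.15, 0.25, 0.35 or 0.40 SD at r = 0.3, 0.5, 0.7 or 0.8.

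**4. Precision.** The standard error of the arm difference is √(2/n) unadjusted and √(2/n) × √(1 − r²) with baseline adjustment. The 95% half-width is 1.96 times this.

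| r | √(1 − r²) | Narrowing | Half-width, 13 per arm (unadjusted 0.77 SD) | Half-width, 10 per arm (unadjusted 0.88 SD) |
|---|---|---|---|---|
| 0.3 | 0.954 | 5% | 0.73 | 0.84 |
| 0.5 | 0.866 | 13% | 0.67 | 0.76 |
| 0.7 | 0.714 | 29% | 0.55 | 0.63 |

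**5. Small-sample check.** 20,000 trials per setting were simulated with normal data and no true effect, using t intervals.

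- At 13 per arm the mean half-width falls from 0.801 to 0.709 (11%) at r = 0.5, and from 0.802 to 0.586 (27%) at r = 0.7.
- At 10 per arm it falls from 0.926 to 0.828 (11%) and from 0.925 to 0.683 (26%).
- So a little of the large-sample gain is lost.
- Over all trials at 13 per arm, the unadjusted difference has bias of about zero and coverage of 94.9% (r = 0.5) and 95.1% (r = 0.7).
- In the trials at 13 per arm with a baseline difference above 0.5 SD, unadjusted coverage is 88.6% (r = 0.5) and 84.1% (r = 0.7). With adjustment it is 94.8% and 94.2%.

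**6. Arm-wise intervals.** With equal SDs and 13 per arm, each mean has half-width 1.96 / √13 = 0.54 SD. Two such intervals separate only when the means differ by about 1.09 SD, whereas the half-width for the unadjusted difference is 0.77 SD.

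**The case against.** The strongest reply is that the article condenses a fuller protocol and that a covariate model is often left to an analysis plan. The article never calls the comparison unadjusted, and its intervals may be meant for the difference, which would fit the Outcomes section's language about effects. This stands against any claim that the plan has committed itself to arm-wise or unadjusted results. It does not remove the point: the method the article does name contains no between-arm quantity, while its own question is comparative.

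A reader might also infer that chance imbalance will distort or bias the comparison. The documents do not support that. Allocation is randomised, so the unadjusted difference is unbiased, and a proper interval for it already allows for chance imbalance. Nor does a baseline difference pass in full into follow-up; it is scaled by r.

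Two further replies stand and limit the weight of the point. First, the gain is only about 5% at r = 0.3, and nothing in the article rules out so low a correlation in a mixed cancer population measured 18 weeks apart. Second, the trial disclaims power for these outcomes, plans no tests on them, and sets its traffic-light criteria on adherence, retention, recruitment and satisfaction. Descriptive reporting is a legitimate choice for a pilot. Even so, low power is a reason to use the collected baseline values rather than leave them out.

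**Conclusion.** The point holds as a low-severity improvement to the secondary outcomes, not as an error in the plan. The Analysis section should say which interval it means and use the T1 value where one exists.

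The benefit is an interval for the difference that is narrower by about 5%, 13% or 29% at assumed r of 0.3, 0.5 or 0.7, slightly less in samples this small. It also protects the result in the roughly one trial in five (about one in four at 10 per arm) where a given measure starts more than 0.5 SD apart. Adjusted intervals remain wide, at about ±0.55 to ±0.84 SD over these scenarios, so they should still not be read as evidence of efficacy. The figures rest on the assumed correlations, roughly normal outcomes, equal SDs in the two arms, and no stratification by a prognostic factor.

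**What to change.** Add one paragraph to the Analysis section:

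- For each continuous outcome with a T1 value, report the between-arm difference at T2 and at T3 with its 95% confidence interval, from a linear model containing arm and the T1 value of the same measure.
- State that this is estimation only, without hypothesis tests.
- Keep the arm-wise descriptive table, with medians and quartiles for skewed outcomes. Where the linear model fits poorly, give a bootstrap or transformed-scale interval for the difference.
- For health care utilization, which has no T1 value, report the unadjusted between-arm difference with its interval.

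The cost is the paragraph, a few lines of Stata and one degree of freedom per model. No extra patients or assessments are needed, and the primary outcome, the sample size and the traffic-light criteria stay as they are.
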